**PROTOCOL INFORMATION REQUIRED**

The following sections below **must** be included in the CPRD ISAC research protocol. Please refer to the guidance on ‘***Contents of CPRD ISAC Research Protocols***’ ([www.cprd.com/isac](http://www.cprd.com/isac)) for more information on how to complete the sections below. Pages should be numbered. All abbreviations must be defined on first use.

| **Applicants must complete all sections listed below**  **Sections which do not apply should be completed as ‘*Not Applicable’*** |
| --- |
| 1. **Study Title§**   **§***Please note:**This information will be published on CPRD’s website as part of its transparency policy*  The use and protective effect of antibiotics against complications of infection in patients in primary care: a cohort study using linked data from CPRD, HES and ONS |
| 1. **Lay Summary (Max. 200 words)§**   **§***Please note:**This information will be published on CPRD’s website as part of its transparency policy*  We all rely on antibiotics to treat infections, but our supply of antibiotics that work is running out. Some bacteria that cause infections have become highly resistant to antibiotics. This “antibiotic resistance” is much more likely to happen if we use antibiotics too often when we don’t really need them. In the NHS, three-quarters of all antibiotics are prescribed by general practitioners (GPs). Often antibiotics are the right treatment for patients but sometimes patients are prescribed antibiotics for viral infections like coughs and colds, where antibiotics don’t work. Some patients receive lots of antibiotics, others get them very rarely. Some GPs seem to prescribe antibiotics more often than others. The aim of this study is to use anonymous GP medical records (so individual patients can’t be identified) to find out more about when and why antibiotics are prescribed in General Practice. We want to understand why some patients get antibiotics more often than others and when patients really need an antibiotic. We will use our work to develop computer simulations to help GPs decide when to prescribe antibiotics. By reducing the number of times that antibiotics are prescribed unnecessarily we will help to keep our current antibiotics working for longer. |

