| 1. **Objectives, Specific Aims and Rationale**   *Objective*  To investigate the use of antibiotics and their protective effect against complications of infection to inform the development of risk prediction models to guide antibiotic treatment decisions for suspected infection in primary care.  *Aims*   1. Estimate the incidence of i) GP consultations for infection and ii) antibiotic prescriptions by: age-group, gender, SES, ethnicity, selected co-morbidities, obesity and smoking status 2. Describe antibiotic prescribing patterns linked to the reason for the prescription by: age-group, gender, SES, ethnicity, selected co-morbidities, obesity and smoking status 3. Estimate the incidence of adverse outcomes in the following 28 days including: hospital admission for infection; A&E admission; re-consultation for infection; re-consultation for antibiotic side-effects (rash, nausea, …) and death for patients with a GP consultation for i) respiratory tract infection ii) urinary tract iii) skin/soft tissue infection, comparing patients with each listed age/co-morbidity group (including smoking status and obesity) to non-comorbid patients 4. Estimate the number of patients needed to treat with antibiotics to avoid one infection-related adverse outcome, comparing the results for each age/co-morbidity group to non-comorbid patients 5. Develop risk prediction tools to support clinical decision making and communication with patients   *Rational*  We have previously shown that more than half of all antibiotic prescriptions in primary care are issued to less than 10% of patients, and that this 10% of patients have high levels of co-morbidity.1 Targeting such high-frequency users of antibiotics in antimicrobial stewardship programmes might provide opportunities for a more effective intervention approach. Underlying this hypothesis is the assumption that it might be safe and feasible to reduce prescribing in patients with the highest levels of antibiotic prescribing, many of whom have co-morbidity.  To investigate whether higher rates of antibiotic use are likely to be justified in higher risk patients compared to patients who lack these risk factors, we will undertake a series of studies to investigate which patients in terms of age, gender, SES, ethnicity, selected co-morbidities, obesity and smoking get the most antibiotics. We will determine which patients are most likely to receive antibiotics for which infections and relate this to national guidance on antibiotic prescribing. To estimate whether the protective effect of antibiotics differs according to the patient’s age and the presence of co-morbidity, obesity or their smoking status, we will estimate the risk of infection related adverse-outcomes, comparing patients who have been treated with antibiotics to those who have not been treated with antibiotics for each of these groups. We will use these estimates to calculate the number of patients who need to be treated with antibiotics to avoid one infection-related adverse outcome (NNT), accounting for age, gender, SES, ethnicity, co-morbidity, obesity and smoking status. This will inform the development and validation of individualised risk-prediction models to support clinical decision-making and patient communication around the need for antibiotic treatment for suspected infection in primary care. |

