| 1. **Exposures, Health Outcomes§ and Covariates**   **§***Please note:**Summary information on health outcomes (as included on the ISAC application form above) will be published on CPRD’s website as part of its transparency policy*  *Exposure*  Exposures will include i) prescription of an antibiotic ii) GP consultation for suspected infection (see Appendices: Table 1 – Codelist for antibiotics, Table 2 – Codelist categorising indications for antibiotic use and Table 3 – Codelists to identify patients with suspected respiratory tract, urinary tract or skin/soft tissue infection)  *Health Outcomes*  The following outcomes (within 28 days of presentation in primary care) will be separately considered for analysis:   - Re-consultation for the same type of infection (CPRD; see Appendix Table 3) - Re-consultation for a side effect of antibiotic treatment (CPRD; see Appendix Table 4a –side effects of antibiotic treatment) - Complications of infection in primary or secondary care (CPRD and inpatient HES; see Appendices: Table 4b and 4c – complications of infection; depending on the indication) - Admission to Accident & Emergency (HES A&E) - All-cause hospitalisation (inpatient HES) - All-cause mortality (CPRD, HES and ONS)   We will undertake a sensitivity analysis to investigate the impact of excluding outcomes that occur on the same day as the exposure. The impact of different time windows will be explored, informed by a literature review on the natural history of the duration of different infections.  *Covariates*  We will include the following covariates:   - Age (classified as 0-4, 5-17, 18-44, 45-64, 65-84, 85-94 and 95+, years of age inclusive) - Sex (female and male) - Index of Multiple Deprivation (IMD; 1-5) - Co-morbidities (coded as indicator variables based on national guidance from Public Health England3 and feasibility1; see Appendix Table 5 for comorbidity code list)   - Diabetes   - Chronic Kidney Disease (CKD)   - Chronic Obstructive Pulmonary Disease (COPD)   - Asthma - Obesity - Smoking status15 - Season (months or quarters) and year - Ethnicity   We will undertake a sensitivity analysis of the impact of coding co-morbidities as binary indicator variable and as total number of co-morbidities. |

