| 1. **Data/ Statistical Analysis**   *1. Estimate the incidence of i) GP consultations for infection and ii) antibiotic prescriptions*  For every patient in cohort 1, data on all consultations for infection and antibiotic prescriptions occurring within the study period will be extracted. We will estimate the incidence of GP consultations for infection and antibiotic prescriptions. This will be done for all consultations and prescriptions, and then separately for each category of infection and each class of antibiotics, based on chapter 5.1 of the British National Formulary (BNF) (see Appendix Tables 1 & 2). The denominator will be estimated as total person-time contributed by patients in the cohort during the study period. We will use Poisson regression to estimate the adjusted rate of consultation and prescription, taking account of the effect of age, gender, SES, ethnicity, selected co-morbidity, smoking and obesity. Random effects will be included to take account of clustering of observations by practice. Rates will be assessed for overdispersion by additionally fitting a negative binomial model and testing for alpha greater than zero via a likelihood-ratio test. If rates are found to be overdispersed, the negative binomial model will be used instead of a Poisson model. Adjusted rate ratios will be presented with 95%-confidence intervals.  *2. Describe antibiotic prescribing patterns linked to the reason for prescription*  The overall number of antibiotic prescribing episodes will be calculated for each patient individually, counting all recorded prescriptions between 1st April 2007 and 31st December 2015. For each episode, a clinical indication will be ascertained. Read codes for a diagnosis or symptom of infection recorded on the same day as the antibiotic prescription will be assumed to represent an indication for the prescription. Where more than one possible indication within the same type of infection is recorded on the day of prescription, the more granular code will be used. If multiple indications across different types of infection are recorded, the prescription will be labelled as having multiple indications. Conversely, if no infectious indication for a prescription was found, the prescription will be labelled as having no infectious indication and we will look for any non-infectious codes associated with the date of antibiotic prescription. The ten most common indications will be established and compared to the same numbers for the period from 1998-2001.14 This approach will be replicated for each class of antibiotics based on chapter 5.1 of the BNF. Patterns of repeat consultation or prescription during episodes of infection which may be prolonged will be investigated for each antibiotic prescription extracted in objective 1. We will define a new episode as a consultation or prescription recorded at least 28 days after any previous consultation for infection or antibiotic prescription. We will undertake sensitivity analyses to investigate the impact of using different time periods to define an episode. We will also examine the use of regular (prophylactic) antibiotic treatment.  Proportions and appropriate 95%-confidence intervals will be calculated and all results will be stratified by age-group, gender, SES, ethnicity, selected co-morbidity, obesity and smoking status. Descriptive data will be displayed graphically.  *3. Estimate the incidence of adverse outcomes in the following 28 days*  For each of the selected clinical infection syndromes in the nested cohort study, events in CPRD, HES and ONS will be searched for all adverse outcomes of interest (see *M.* Exposures, Health Outcomes§ and Covariates). Crude incidence rates of for each outcome will be calculated for patients who were treated (exposed) and not treated (unexposed) with an antibiotic. The denominator will be estimated as the total person-time contributed by patients at risk of each adverse outcome, taking account of the fact that this will be different for each outcome. For example, exposed and unexposed patients cannot consult General Practice if they have been admitted to hospital and should therefore not contribute to the denominator during this period when estimating rates of GP re-consultation in the 28 days following consultation for infection. A Poisson regression model will be used to estimate adjusted rates of adverse outcomes in each group, controlling for age, gender, socio-economic status, ethnicity, co-morbidity, obesity and smoking status and assessing for interaction between age and co-morbidity. Random effects will be included to take account of clustering of observations by practice. If the outcomes are overdispersed, negative binomial models will be used instead of Poisson models. Adjusted rate ratios will be presented with 95%-confidence intervals.  *4. Estimate the number of patients needed to treat with antibiotics to avoid one infection-related adverse outcome*  For each clinical infection syndrome-related adverse outcome identified in objective 3, the odds of that outcome in the 28 days following consultation for those treated with antibiotics (unexposed) and not treated with antibiotics (exposed) will be estimated using logistic regression. We will calculate adjusted odds ratios for the protective effect of antibiotics, adjusting for age, gender, SES, ethnicity, year/season, co-morbidity and the probability of receiving antibiotic treatment (see *O. Plan for addressing confounding*) and assessing for interactions with age and co-morbidity. We will use mixed models to adjust for clustering at a practice level and to take account of clustering of observations within a patient due to repeat episodes of infection. Where there is a significant effect of antibiotics between treated and untreated patients, the NNT or NNH to prevent one individual from developing an adverse outcome is calculated as *1/(absolute risk difference)*. A significant effect will be defined by a p-value < 0.05 for the coefficients of antibiotic treatment and its interactions. To avoid an arbitrary cut-off point, p-values close to 0.05 will also be assessed but discussed separately. The NNT will then be used to assess the clinical relevance of any significant differences found. Whilst the relative risk reduction (RRR) may be similar, the NNT may be different due to differing background risk. This will be explored.  *5. Develop risk prediction tools to support clinical decision making*  For each cohort (i.e. for each of the clinical syndromes of UTI, RTI and SSTI), we will develop a logistic regression risk model to predict the risk of adverse outcomes if patients are treated versus not treated with antibiotics. Models will be developed on a random sample of 80% of the observations within a cohort, reserving 20% of the data to estimate the model’s predictive performance.  A negative outcome will be defined as the occurrence of any of the following within 28 days following the index consultation: hospital admission for infection or complication; re-consultation for infection; A&E admission; death. Antibiotic treatment will be defined as a prescription of an antibiotic on the day of consultation for clinical syndrome. Risk factors will be selected based on the analyses outlined in objectives 1-4 and broadly grouped into: socio-demographic variables, co-morbidity and clinical presentation. Biologically plausible interactions between risk factors and age and between risk factors and co-morbidities will be examined.  Whereas age and sex will be forced into the model, other risk factors will be added in order of their significance in objective 4. Risk factors will be kept in the model if they improve the predictive performance of the model as defined by model discrimination and model calibration.17 For example, a risk factor will be used in the model if it improves discrimination and/or calibration. If a variable improves discrimination but reduces calibration, it will still be included in the model, but will be omitted if it increases calibration at the cost of discrimination.  Model discrimination, i.e. the model’s ability to correctly identify patients with and without an outcome, will be estimated using the concordance (c) statistic.18 The c statistic represents the probability that between two randomly chosen patients, one with the outcome and one without, the model assigns a higher score to the patient with the outcome. As a second measure, model calibration will be assessed using the Hosmer-Lemeshow test.18 We will additionally assess model calibration graphically for reasons for poor calibration by comparing the mean observed outcome in deciles of predicted risk. In this calibration plot, the intercept indicates the extent to which predictions are systematically too low or too high, while the slope reflects overfitting of the model.  For each model, we will estimate the internal validity of discrimination and calibration estimates using cross-validation with bootstrap subsampling based on 1000 iterations. In a secondary analysis, we will assess model performance in subgroups by age, sex and co-morbidity.  Finally, we will develop a simplified scoring system using the risk factors in the model,17 assigning the total score to a specific absolute risk of adverse outcomes in the 28 days following consultation, comparing outcomes if an individual is treated versus not treated with antibiotics. We will assess the predictive performance of the risk scores using the approaches outlined above. |

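### The step 5 decision tool leaves out re-consultation for antibiotic side-effects, so its treated-versus-untreated comparison does not show treatment harm seen in general practice

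*Protocol*

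**What the plan says.** **Outcomes.** Aim 3 (Objectives, Specific Aims and Rationale) includes "re-consultation for antibiotic side-effects" among the adverse outcomes to be estimated over 28 days. The Health Outcomes list in Exposures, Health Outcomes and Covariates repeats it as "Re-consultation for a side effect of antibiotic treatment", with its own code list in Appendix Table 4a.

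**Separate analyses.** Step 3 of Data/Statistical Analysis estimates the rate of each outcome by treatment group. Step 4 provides, where the antibiotic effect is significant, for "the NNT or NNH to prevent one individual from developing an adverse outcome".

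**The tool.** Aim 5 is to "Develop risk prediction tools to support clinical decision making and communication with patients". Step 5 builds one logistic model per infection cohort "to predict the risk of adverse outcomes if patients are treated versus not treated with antibiotics". It gives a closed definition of the negative outcome: "hospital admission for infection or complication; re-consultation for infection; A&E admission; death". The simplified score then assigns an absolute 28-day risk, "comparing outcomes if an individual is treated versus not treated with antibiotics".

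**Purpose.** The Lay Summary states the intended benefit: "By reducing the number of times that antibiotics are prescribed unnecessarily", current antibiotics should stay effective for longer.

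**The concern.** Of the outcomes the protocol defines, side-effect re-consultation is the one that treatment is expected to cause. It is analysed on its own in steps 3 and 4, then left out at the point where the two options are put before the GP and the patient. An excess of such visits after treatment would be missing from the treated side of the display, with nothing to offset it on the untreated side.

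This matters most for patients at low risk. Their expected benefit is small, so a modest side-effect risk is large beside it. These are also the consultations in which a tool meant to curb unnecessary prescribing has most to offer. The definition is written out in full in the protocol, so it is not a detail left open for a later analysis plan.

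**Working it through.** No figure in the protocol is in dispute. The check is a comparison of the outcome lists, followed by an illustration of scale.

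**1. Side-by-side comparison**

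| Outcome | Aim 3 | Health Outcomes list | Step 5 composite |
|---|---|---|---|
| Re-consultation for infection | yes | yes (same type of infection) | yes |
| Re-consultation for side-effects | yes | yes | **no** |
| A&E admission | yes | yes | yes, any cause |
| Hospital admission | for infection | all-cause | for infection or complication |
| Death | yes | all-cause | yes, any cause |

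A side-effect that leads to A&E or death is therefore inside the composite. One handled by the GP, such as the rash or nausea that aim 3 gives as examples, is not. An inpatient admission for a drug reaction counts only if it also involves A&E or death, or is coded as an infection or complication.

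**2. Is the harm carried into the tool by another route?** Step 4 can yield a number needed to harm, but one outcome at a time and only where the effect is significant. Step 5 uses the earlier objectives to select risk factors. Study Design says that objective 5 will synthesise objectives 1 to 4, but step 5 names no side-effect output in either the model or the score.

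**3. Scale of the benefit shown (illustration)**

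Inputs from Sample size considerations: outcome risk 2.4% (found earlier for pneumonia) and an average antibiotic odds ratio of 0.69. Taking 2.4% as the untreated risk is an assumption.

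- Untreated odds: 0.024 / 0.976 = 0.02459
- Treated odds: 0.69 × 0.02459 = 0.01697
- Treated risk: 0.01697 / 1.01697 = 0.01668, or 1.67%
- Absolute difference: 2.40% − 1.67% = 0.73 percentage points
- NNT: 1 / 0.00732 = about 137

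The step 5 composite includes re-consultation, which the protocol itself treats as more common, so higher untreated risks are plausible. With the same odds ratio and assumed risks:

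| Untreated risk | Treated risk | Difference (points) | NNT |
|---|---|---|---|
| 2.4% | 1.67% | 0.73 | 137 |
| 5% | 3.50% | 1.50 | 67 |
| 10% | 7.12% | 2.88 | 35 |
| 20% | 14.71% | 5.29 | 19 |

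The protocol gives no rate of side-effect re-consultation in either group, so there is nothing to set against these figures. The table shows only the size of benefit beside which the missing harm should be read.

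**The case against.** **Harm is analysed elsewhere.** This is true of the study: step 3 gives side-effect rates by treatment, and step 4 can give a number needed to harm. It is not true of the tool, and the tool is what the GP and patient will see.

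**An infection-only composite is defensible.** The overall objective concerns protection against complications of infection, and a rash visit does not belong in one endpoint with death. This stands, and it is a reason to keep the composite and report side-effects beside it. It is not a reason to leave them out.

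**Objective 5 is only prediction.** The section on comparison groups says that objective 5 attempts no comparison. Step 5 nevertheless compares treated with untreated risk, and Plan for addressing confounding places inference about the effect of treatment in objectives 4 and 5.

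**Stronger readings that the protocol does not support.**

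- A reader might infer that the tool counts nothing but outcomes antibiotics can prevent. A&E admission and death carry no restriction by cause, so serious drug harm that reaches either is counted.
- A reader might infer that the finished tool is biased towards prescribing. The confounding section says that confounding by indication tends to understate the protective effect. What remains of it after adjustment pushes the other way, so the net direction is open.
- A reader might subtract a side-effect excess from the 0.73 points and conclude that treatment does net harm in some patients. Any such change of sign would follow from an assumed excess. It would also weigh a rash visit equally with a death and ignore overlap between events.
- A reader might add that step 5 names complications only through hospital admission, whereas the Health Outcomes list includes those in primary care. That omission would drop events antibiotics may prevent, so it would understate benefit. Whether it is a real omission depends on appendix code lists that are not shown.

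**Conclusion.** The point holds in a limited form. Step 5 omits, without explanation, an outcome that aim 3 and the Health Outcomes list both define, and it does so in the one product that compares treatment with no treatment for an individual patient. As written, the score would not show side-effects managed in general practice. Provided that treated patients have more side-effect re-consultations than comparable untreated patients, it looks more favourable to treatment than a score that shows them.

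The size of that difference cannot be given. The 0.73-point benefit is an illustration that rests on a pneumonia risk taken as the untreated risk and on an odds ratio averaged over other complications. The conclusion concerns what the tool leaves unseen. It does not establish the tool's overall bias, or that treatment is not worthwhile for any group.

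**What to change.** Leave the step 5 composite as it is. For each of the three cohorts, add a second 28-day model for side-effect re-consultation (Appendix Table 4a), with the same development sample, performance measures and internal validation. In the simplified score, show the predicted side-effect risk with and without treatment beside the composite risk. If the authors prefer not to do this, step 5 should give the reason and say how side-effect results will reach the user.

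Separately, reconcile step 5's wording on complications with the Health Outcomes list, so that it is clear whether complications managed in primary care count.

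The cost is three further models on an outcome already defined and due to be extracted for steps 3 and 4, plus some wording. There are two drawbacks. The score has two outputs to explain instead of one. Side-effect codes such as rash need care in the skin/soft tissue cohort, where they may reflect the infection itself.
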